## Assignment of interventions: Blinding

### Who will be blinded {17a}

Full blinding of the clinical team cannot be ensured because children randomised to the control arm may display spontaneous movements and/or breathing. For this reason, the study team will be prohibited from participating by any means in the clinical care of the participant. On top of that, the statistical analysis and long-term outcome assessment staff are blinded to the study arm, and aggregate outcome data will be restricted to an unblinded statistician and the data safety monitoring board.

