#### Secondary outcomes

Data for the secondary and exploratory outcome measures will primarily be collected during the acute phase of disease, when patients are admitted to the PICU. Ventilator settings and respiratory system parameters will be read from the ventilator. Blood sampling will be done to assess pCO_2_ and pH; to calculate the PaO_2_/FiO_2_ ratio and the OI (calculated by [mean airway pressure * FiO_2_ * 100]/PaO_2_) the PaO_2_ needs to be determined in arterial blood samples. The SpO_2_/FiO_2_ ratio can be calculated if SpO_2_ < 98%. If no indwelling arterial line is present, the OSI  ([mean airway pressure * FiO_2_ * 100]/SpO_2_) is used. Haemodynamic parameters are read from the patient monitor; cumulative fluid balance is calculated as the sum of daily fluid balance; it is normalised to actual bodyweight. Calculation of the non-respiratory PELOD-2 requires the Glasgow Coma Score, pupillary reaction to light (both reactive/both dilated), lactate, mean blood pressure, creatinine, white blood cell count, and platelets. Blood sampling will be done using the indwelling arterial line or central venous line. The pRIFLE criteria require assessment of serum creatinine and urine output as described elsewhere [28].

Published criteria are used to study the prevalence of critical illness polyneuropathy and myopathy (CIPNM) [19, 31]. The diagnosis CIPNM is present if the patient has possible limb weakness (i.e. inability to raise the limbs against gravity upon a stimulus), electrophysiological evidence of axonal motor and sensor polyneuropathy, and if the patient is difficult to wean from the ventilator and no apparent cause is present. Strength of muscle limbs will be assessed daily by the attending physician as part of the routine clinical examination after 48 h after randomisation until the moment of discharge from the PICU. If this is present and the patient cannot be weaned of the ventilator, a paediatric neurologist is asked for consultation and electromyographic investigations are indicated. The latter two are part of routine care in patients with unexpected muscular weakness. Only then the diagnosis of CIPNM is confirmed or refuted. Centre for Disease Control definitions for ventilator-associated pneumonia (VAP) will be used [32]. Both CIPNM and VAP will be assessed daily by the attending physician as part of the routine clinical examination 48 h after randomisation until the moment of discharge from the PICU.

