### Interim analyses {21b}

The data safety monitoring board (DSMB) will monitor the study for efficacy and adverse events. Two interim analyses are planned after the inclusion of 50 and 100 patients respectively. For safety reasons, the study will be terminated prematurely if there is a significant increase in critical illness polyneuropathy and myopathy in these interim analyses (i.e. a threefold increase in prevalence) or for futility if there is no difference in the primary outcome measure.

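### CIPNM, the safety-stopping outcome, and VAP are ascertained by an attending physician who cannot be fully blinded, with no masked step, so differential referral or calling could create or hide a difference between arms

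*Protocol article*

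**What the plan says.** The Secondary outcomes part of *Plans for assessment and collection of outcomes {18a}* names the assessor: "Both CIPNM and VAP will be assessed daily by the attending physician as part of the routine clinical examination", from 48 h after randomisation to PICU discharge. It builds CIPNM ascertainment in steps:

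- Strength: "Strength of muscle limbs will be assessed daily by the attending physician as part of the routine clinical examination after 48 h after randomisation".
- Referral: "If this is present and the patient cannot be weaned of the ventilator, a paediatric neurologist is asked for consultation and electromyographic investigations are indicated".
- Diagnosis: "Only then the diagnosis of CIPNM is confirmed or refuted".

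For VAP, "Centre for Disease Control definitions for ventilator-associated pneumonia (VAP) will be used", with no confirmation step.

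*Who will be blinded {17a}* concedes that "Full blinding of the clinical team cannot be ensured because children randomised to the control arm may display spontaneous movements and/or breathing". Its remedy is to keep the study team out of clinical care. The roles it lists as masked are limited: "the statistical analysis and long-term outcome assessment staff are blinded to the study arm".

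*Interim analyses {21b}* stops the trial for safety, at looks after 50 and 100 inclusions, if CIPNM rises significantly, which it glosses as "a threefold increase in prevalence". CIPNM and VAP are also secondary outcomes under *Outcomes {12}* and recorded adverse events under *Adverse event reporting and harms {22}*.

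**The concern.** The person who judges limb strength and calls VAP belongs to the group that the article says cannot be fully blinded, and may have watched the child lie paralysed or move for 48 h. The article names muscle weakness as a risk of prolonged rocuronium infusion (*Intervention description {11a}*), so knowledge of the arm could change how hard a physician looks for it.

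For CIPNM the weak point is referral. Electromyography can reject a false suspicion among referred children, but it cannot recover a true case that was never referred. The onset of weaning, which bears on the second referral condition, is also at the attending physician's discretion (*Relevant concomitant care {11d}*). At stake are two secondary safety comparisons and a count on which the trial can be stopped.

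**Working it through.** **The passages side by side.** Section {18a} makes the attending physician the assessor of strength, CIPNM and VAP. Section {17a} places that physician in a team that cannot be fully blinded and lists as masked only the analysis and long-term outcome staff. Keeping the study team out of care does not mask the attending physician. Unmasked ascertainment is thus fixed by the text and is not merely left unsaid.

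**No figure in the plan to reproduce.** The article gives no power or error rate for the CIPNM rule, so the calculation below is illustrative.

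*Inputs from the article:* looks at 50 and 100 inclusions, so about 25 and 50 per arm; a threefold threshold; a cited frequency of ICU-acquired weakness of 55/203,875 = 0.027%, printed as 0.03%.

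*Assumptions:* the same true CIPNM risk p in both arms (no drug effect), with p = 2%, 4% or 10% besides the cited figure; detection probabilities s_R on rocuronium and s_C on placebo of 90/90, 90/45 and 90/30 per cent. The article supplies neither these risks nor these detection rates.

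*Expected observed ratio:* (p × s_R)/(p × s_C) = s_R/s_C. This gives 0.90/0.90 = 1.0, 0.90/0.45 = 2.0 and 0.90/0.30 = 3.0. The last equals the stopping threshold with no drug effect.

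*Chance of crossing:* let X ~ Binomial(n, p·s_R) be the rocuronium count and Y ~ Binomial(n, p·s_C) the placebo count. The event is X ≥ 3 and X ≥ 3Y. Its probability is the sum of P(X = x)·P(Y = y) over all such pairs.

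| Assumed true risk, n = 50 per arm | 90/90 | 90/45 | 90/30 |
|---|---|---|---|
| 0.027% (cited) | about 0 | about 0 | about 0 |
| 2% | 4.7% | 5.7% | 5.9% |
| 4% | 12.5% | 20.9% | 23.7% |
| 10% | 8.2% | 36.8% | 54.5% |

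At the first look (n = 25 per arm) and 4% risk the figures are 4.6%, 5.5% and 5.7%.

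*Opposite direction:* with 45% detection on rocuronium and 90% on placebo, at 4% risk and n = 50, the chance falls from 12.5% to 2.8%. Under-referral after paralysis would thus hide an excess.

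*If the word significant means a formal test:* require two-sided Fisher p < 0.05 as well. At 50 per arm, 3 against 0 gives p = 0.24 and 5 against 0 gives p = 0.056; 6 against 0 is the first such split to qualify (p = 0.027). At 4% risk the three probabilities become 0.15%, 0.37% and 0.50%. Section {21b} names no test, so this reading is also an assumption.

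**VAP.** The article offers nothing from which to size a bias. The point rests on an unmasked assessor applying a definition with no described confirmation.

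**The case against.** The strongest case against has four parts.

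*Existing safeguards.* The article gives an explicit limb criterion (raising the limbs against gravity), the same daily schedule in both arms, assessment only after the planned infusion has ended, a two-condition trigger for referral, electrophysiological confirmation and a published VAP definition. This stands in part. Suspicion alone cannot produce a confirmed CIPNM case. But a common schedule equalises how often a child is examined, not the threshold applied, and starting after 48 h does not undo what was seen during the infusion.

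*Size.* The article calls CIPNM in children very rare, and at 2% risk or below differential detection hardly changes the chance of crossing. This stands. The 0.03% figure covers all PICU admissions, so it may understate the risk in ventilated children with moderate-to-severe PARDS, but nothing in the article supports 4% or 10%. Even with equal detection the chance is 12.5% at 4% risk, so much of the crossing probability comes from a loose rule and not from unmasked assessment.

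*Direction.* A reader might infer that unmasked assessment will produce a spurious CIPNM excess on rocuronium and stop the trial. The article does not support that. It describes the work-up as routine for unexpected weakness, and a physician who saw the paralysis might expect weakness and refer less.

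*Level of detail.* Form fields and scripts usually sit in the full protocol, which is not shown. That is fair, and their absence is not the finding. The finding is that the article assigns the assessor and also states that this assessor's team cannot be fully blinded.

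**Conclusion.** The concern holds as a design weakness in two secondary safety outcomes. Who is referred for CIPNM testing, and who is called as having VAP, is decided by someone who may know the arm, and no masked step is stated. A CIPNM difference could be created or concealed; the direction of any VAP bias is unknown. The primary outcome, a parental questionnaire at 12 months, does not depend on these assessments.

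The consequence for stopping is conditional. It is negligible at the cited frequency and small at 2%. It is appreciable at 4% to 10% if a bare threefold ratio is enough, and below 1% at 4% if Fisher significance is also needed. All of this rests on assumed detection rates. The change is worth making because it is cheap and protects a count that can end the trial, not because a false stop has been shown to be likely.

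**What to change.** Leave clinical referral exactly as section {18a} states it, and change only what is recorded and how the trial endpoints are classified:

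1. Record the limb-against-gravity check (yes/no) and wean status daily for every child in both arms. Report by arm the children who met the article's referral criteria but were not referred.
2. Have the routine reader classify the electromyography result used for the CIPNM endpoint without being given the treatment arm.
3. For analysis, derive VAP by a fixed algorithm from recorded elements of the cited definition and the routine radiology report, not from the attending physician's call.

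The cost is a few CRF fields and a derivation script, with no extra staff or procedures. The limitation is that the bedside strength check itself stays unmasked, so the bias is reduced and made visible but not removed.

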#### Exploratory outcome measures

Prevalence of drug withdrawal symptoms and delirium will be assessed according to local scoring system. Assessments will be done daily. Ventilator-free days at day 28 (VFD) is defined as the number of days within 28 days that a subject is alive and free of MV [34]. Patients will be assigned 0 VFD if they remained intubated or died prior to day 28 without remaining extubated for more than 24 h, or if they were cannulated for ECLS. Mortality is defined as PICU mortality and mortality 90 days after PICU discharge. The Pediatric Cerebral Performance Category and Pediatric Outcome Performance Category are calculated as described elsewhere [35].

All handling of personal data will be done according to the European General Data Protection Regulation. All data and samples will be collected and stored under a pseudonym. The subject’s identification code list will be available to the project leader and the investigator. Data will be collected by the research nurses and/or site-investigators. Study data were collected and managed using Research Electronis Data Capture (REDCap) electronic data capture tools hosted at UMCG [36, 37]. Data will be stored for 15 years. Samples will be stored at the University Medical Centre Groningen.

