**Methods:**

This is a phase IV, multicentre, randomised, double-blind, placebo-controlled trial performed in level-3 PICUs in the Netherlands. Eligible for inclusion are children younger than 5 years of age requiring invasive mechanical ventilation with positive end-expiratory pressure (PEEP) ≥ 5 cm H_2_O for moderate-to-severe PARDS occurring within the first 96 h of PICU admission. Patients are randomised to continuous infusion of rocuronium bromide or placebo for 48 h. The primary endpoint is the cumulative respiratory morbidity score 12 months after PICU discharge, adjusted for confounding by age, gestational age, family history of asthma and/or allergy, season in which questionnaire was filled out, day-care and parental smoking. Secondary outcomes include respiratory mechanics, oxygenation and ventilation metrics, pulmonary and systemic inflammation markers, prevalence of critical illness polyneuropathy and myopathy and metrics for patient outcome including ventilator free days at day 28, length of PICU and hospital stay, and mortality

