##### Exploratory outcome measures

These include use of (non-) pulmonary ancillary treatment (e.g. steroids, inhaled drugs, prone positioning) and HFOV, daily cumulative dosage sedatives and analgesics, prevalence of drug withdrawal symptoms and delirium, ventilator-free days at day 28 (VFD), length of MV, length of PICU stay and mortality. We will also explore changes in Pediatric Cerebral Performance Category and Pediatric Outcome Performance Category.

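### A child who dies before day 28 after more than 24 h off the ventilator keeps a positive ventilator-free-day score and can equal or outscore a longer-ventilated or ECLS survivor

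*Protocol article*

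**What the plan says.** The rule is in the protocol article, under Plans for assessment and collection of outcomes {18a}, Exploratory outcome measures. The base quantity is "the number of days within 28 days that a subject is alive and free of MV". An override follows: a child still on the ventilator scores 0, and so do children who "died prior to day 28 without remaining extubated for more than 24 h, or if they were cannulated for ECLS". Separately, the same paragraph states: "Mortality is defined as PICU mortality and mortality 90 days after PICU discharge".

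The status of VFD differs by place. Objectives {7} lists it as exploratory, and so does the exploratory part of Outcomes {12}: "ventilator-free days at day 28 (VFD), length of MV, length of PICU stay and mortality". The abstract instead places it among the secondary outcomes, as one of the "metrics for patient outcome including ventilator free days at day 28, length of PICU and hospital stay, and mortality".

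**The concern.** VFD combines survival and time off the ventilator in one number. Such a score is easy to read when death takes its lowest value, because a higher score then never conceals a death. Here the zero for death carries a condition. A child who has been extubated for more than 24 h and then dies before day 28 falls outside the override, so the base count applies and the days between extubation and death are credited. The same sentence sets some survivors to zero, namely those cannulated for ECLS. Some deaths can therefore stand above some survivors.

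What is at stake is how a difference between arms would be read. If VFD is compared by the t test or Mann-Whitney test that the article names for non-repeated continuous measures, these scores or their ranks enter directly. An arm with earlier extubation could then look better on VFD even though some of those children died later.

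**Working it through.** The article gives no VFD mean, standard deviation or power to reproduce, so the check is of the scoring rule itself. The days below are illustrative. Each child is assumed to have one final extubation, counted in whole days.

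**Rule as written.** Let *e* be the day of final extubation and *d* the day of death, with *d* < 28.
- Never extubated by day 28, or cannulated for ECLS: VFD = 0.
- Died with *d* − *e* ≤ 1 day: VFD = 0.
- Died with *d* − *e* > 1 day: VFD = *d* − *e*. Days after death are not credited.
- Survived to day 28: VFD = 28 − *e*.

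**Scores.**

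| Course | VFD as written | VFD if every death by day 28 scores 0 |
|---|---|---|
| Extubated day 5, died day 6 | 0 | 0 |
| Extubated day 5, died day 7 | 7 − 5 = 2 | 0 |
| Extubated day 5, died day 20 | 20 − 5 = 15 | 0 |
| Extubated day 5, died day 27 | 27 − 5 = 22 | 0 |
| Extubated day 5, survived | 28 − 5 = 23 | 23 |
| Extubated day 13, survived | 28 − 13 = 15 | 15 |
| Extubated day 18, survived | 28 − 18 = 10 | 10 |
| Extubated day 25, survived | 28 − 25 = 3 | 3 |
| Still intubated at day 28, alive | 0 | 0 |
| ECLS, extubated day 5, survived | 0 | 0 |

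The child who dies on day 20 ties with the survivor extubated on day 13. That child also outscores the survivors extubated on days 18 and 25, the child still intubated, and the ECLS survivor.

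**When a death ties or wins.** Compare a death (*e*, *d*) that keeps credit with a non-ECLS survivor extubated on day *s*. The death scores at least as high when *d* − *e* ≥ 28 − *s*, that is, when *s* − *e* ≥ 28 − *d*. The survivor must have been ventilated longer by at least the number of days that death cut off. For death on day 20 this is 28 − 20 = 8 days, so *s* ≥ 5 + 8 = 13, as in the table. With the same extubation day, *s* − *e* = 0 while 28 − *d* > 0, so the condition always fails: 15 against 23 in the example.

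**Spread of the effect.** Take every whole-day death that keeps credit, with extubation from day 2 onwards (300 combinations). Compare each with survivors extubated on days 2 to 27 or never (27 courses), which makes 300 × 27 = 8,100 pairs. The death scores higher in 2,900 (36%), equal in 300 (4%) and lower in 4,900 (60%). The grid is unweighted. It shows that the inversion is not confined to odd corners, but it does not forecast how often it will occur.

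**The case against.** The strongest reply is that the rule is coherent and fixed in advance. Days alive and off the ventilator is a legitimate quantity, the base count and the override do not contradict each other, and the definition cites a published source that is not at hand. The 24-h clause already gives zero to deaths soon after extubation. VFD is exploratory in the body of the article and plays no part in the primary endpoint, the sample size or the stopping rules. Mortality is a separate outcome and death from any cause is a serious adverse event, so excess deaths would be visible elsewhere.

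Most of this stands, and it limits the weight of the point. It does not remove it. The two mortality measures are not on the 28-day clock of VFD, and neither alters a VFD score.

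Four stronger readings are tempting but unsupported:
- *That a child who dies after extubation in general scores as well as a survivor.* Only days alive count, so a death before day 28 always scores below a survivor extubated on the same day, and a death within 24 h of extubation scores 0.
- *That the number of misranked children can be estimated.* This needs 28-day mortality and the share of deaths that follow more than 24 h of extubation. The article gives neither. Its Background cites mortality up to 40–50% and its Discussion describes the rates as rather low and very variable. Whether a given death is misranked also depends on the survivor it is compared with.
- *That the zero for ECLS is itself an error.* It is an explicit choice that nothing in the article contradicts.
- *That incomplete blinding of the clinical team makes this rule worse than another.* Discretion over weaning would affect any definition of VFD, and the article also calls for a daily extubation readiness test by institutional algorithm.

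**Conclusion.** The point holds in limited form. As written, death before day 28 after more than 24 h off the ventilator is not the worst VFD value. It can tie with or beat survival after longer ventilation, survival with ventilation still running at day 28, or survival after ECLS. A between-arm difference in VFD can therefore favour earlier extubation despite later deaths.

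This rests only on the wording of the rule. The illustrative days show the mechanism, and no mortality assumption is needed. How many children it would touch is unknown. It is a modest but worthwhile correction to a badly fixed scoring rule for an exploratory outcome. The abstract's listing of VFD as secondary means that some readers will give it more weight than the body of the article does.

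**What to change.** Change the definition so that every child who dies on or before day 28 scores 0 VFD, whatever preceded the death. Keep the 24-h criterion only to decide whether an extubation in a survivor counts as successful. Naming day 28 itself also covers a death on that day, which the present wording does not reach. Make the change before outcomes are analysed by arm.

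No death could then score above a survivor. Deaths would still tie at 0 with ECLS survivors and with children still ventilated at day 28. The change does not address those ties, and the write-up should say so.

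The cost is one sentence. No new data are needed, because the times of extubation and death are already required for VFD, length of ventilation and mortality. Mean VFD would be slightly lower in each arm where such deaths occur.

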### Plans to promote participant retention and complete follow-up {18b}

Upon discharge, parents or legal caretakers are asked for their e-mail address and phone number; the personalised link to the web-based questionnaire will be e-mailed to them 3, 6, 9 and 12 months after PICU discharge. If there is no response within 7 days, they will receive a reminder via e-mail to promote participant retention.

### Data management {19}

Data are collected through case report forms in REDCap. Range checks for data values were added in the Code of Federal Regulations (CFR), if possible, to promote data quality. Data management is coordinated by the UMCG researchers and Informatie Management (IM) onderzoek UMCG. All participants receive a trial ID, and the personal details are known only to the researchers, pharmacy, and attending physician. Double data entry and validation are carried out by all participating centres. Monitoring of the data and trial proceedings is coordinated by the UMCG. Monitoring of the data and trial proceedings is carried out per research site before the start of the trial, soon after the start of the trial, and three times a year for the duration of the trial. A close-out visit is carried out after completion of the inclusion period per research site. Trial auditing is carried out only by invitation from the hospital board and its frequency is not specified.

The UMCG, as the coordinating centre, owns intellectual property. The investigators have unlimited access to the final dataset. A newsletter with the study results will be made available on the website of the patient and parent organisations and will be sent to participants upon request. Public access to the data and data sharing is in line with the guidelines of ZonMw (data management plan), the main funder of this trial. Data access is restricted to authorised use only, and access will be granted by the researchers upon reasonable request.

